## Abstract

**Background::**

A proportion of patients with stage IV non-small-cell lung cancer (NSCLC) is predicted to receive third-line treatment. However, currently no standard third-line treatment for NSCLC is available. Anlotinib is an oral, multi-targeted tyrosine kinase (TK) receptor inhibitor, which was approved as a third-line treatment for stage IV NSCLC in China on May 9, 2018. Nevertheless, The objective response rate of patients treated with anlotinib was merely 9.2% and the overall survival was only 3 months compared with the patients treated with placebo. Previous studies have shown that cancer treatment with a combination of chemotherapy with TK receptor inhibitors is effective and safe well tolerated. Therefore, the combination of anlotinib with other chemotherapeutic agents may be an effective treatment strategy for patients with stage IV NSCLC. Oral S-1 is a third-generation fluorouracil derivative; it showed good efficacy and caused relatively low toxicity in patients with NSCLC.

**Methods::**

The purpose of this trial is to evaluate the efficacy and safety of anlotinib combined with S-1 as the third-line treatment for patients with stage IV NSCLC. This is a prospective, phase II clinical trial. We will enroll29 patients with stage IV NSCLC treated with anlotinib plus S-1. Tumors will be assessed using computed tomography prior to treatment, after two, four, and six cycles of treatment, and during follow-up every 3 months until disease progression or death. The primary endpoint is the objective response rate (ORR). The secondary endpoints are progression-free survival, duration of response, proportion of disease control, and safety.

**Discussion::**

The expected outcome of this study is that anlotinib combined with S-1 has tolerable toxicity and better ORR than anlotinibmonotherapy. The results may indicate additional treatment options for patients with stage IV NSCLC.

## Introduction

Lung cancer has far-reaching medical, psychosocial, and economic impacts, and is a burden on the society (Rui et al., 2019).Worldwide, Lung cancer has the highest incidence and high mortality among all types of cancer; 2.1 million new lung cancer cases and 1.8 million deaths were predicted in 2018, which is approximately 1 in 5 (18.4%) cancer deaths (Bray et al., 2018). Non-small-cell lung cancer (NSCLC) accounts for ~85% of all lung cancer cases; majority of the patients are diagnosed after the disease has advanced or has become metastatic (Crinòet al., 2010; Felipet al., 2005; Williamet al., 2009).

The latest National Comprehensive Cancer Network (NCCN) Guidelines recommend gefitinib, lcotinib, erlotinib, and afatinib as the first-line treatment for stage IV NSCLC positive for epidermal growth factor receptor (EGFR) mutation. For patients with anaplasticlymphoma kinase (ALK) rearrangement or ROS proto-oncogene 1 (ROS1) fusion gene, crizotinib is recommended as the first-line treatment. First-line chemotherapy is recommended for advanced NSCLC without a driver gene; second-line treatment is used as a replacement of chemotherapy (National Comprehensive Cancer Network.,2019).Most patients with stage IV NSCLC are predicted to receive a third-line treatment; however, currently, there is no standard third-line treatment for NSCLC.

*K9*

Anlotinib is an oral, multi-targeted tyrosine kinase (TK) receptor inhibitor, which was approved as a third-line treatment for stage IV NSCLC on May 9, 2018 in China. However, the objective response rate (ORR) was only 9.2% and the overall survival (OS) time was prolonged only 3months (China Food and Drug Administration, 2018; Han et al., 2017; Han et al., 2018). The combination of multi-targeted TK receptor inhibitors and chemotherapy is effective and well-tolerated in patients with NSCLC and ovarian cancer (Nishioet al., 2013; Chun et al., 2018).Therefore, anlotinib combined with chemotherapy maybe an effective treatment strategy for patients with stage IV NSCLC. S-1 is an oral fluoropyrimidine agent containing the 5-fluorouracil, the prodrug tegafur, and two enzyme inhibitors, namely, 5-chloro-2,4-dihydroxypyridine and potassium oxonate; it showed good efficacy and caused relatively low toxicity in patients with stage IV NSCLC (Masuda et al., 2018; Iwamoto et al., 2015; Okumura et al., 2013).We designed this study to evaluate the efficacy and safety of anlotinib combined with S-1 as a third-line treatment for patients with stage IV NSCLC.

## Materials and Methods

*Study design*

The study design has been registered with the Chinese Clinical Trial Registry (Number: ChiCTR1900020948).This is a prospective, multicenter, phase II clinical trial. We will enroll 29 patients with cytologically or histologically confirmed stage IV NSCLC. The patients will be treated with anlotinib and S-1; they will undergo computed tomography (CT) before the treatment, after two, four, and six cycles, and during follow-up every 3 months until disease progression or death. If the efficacy is assessed as stable disease (SD), partial response (PR), and complete response (CR) after six cycles, anlotinib will be maintained until disease progression or death. Efficacy will be evaluated according to response evaluation criteria in solid tumors (RECIST); toxicity and side effects will be recorded. Statistical analysis of the data will be conducted using SPSS.

For this study, patients will be recruited from several hospitals in the Sichuan Province. There will be no randomized control group in this study. All patients who meet the inclusion criteria and provide informed consent will participate in the study.

*Objectives*

The primary endpoint is the ORR. The secondary endpoints are progression-free survival (PFS), duration of response, proportion of disease control, and safety.

*Inclusion criteria*

1. Aged 18–75 years

2. Pathologically diagnosed with late NSCLC

3. Eastern Cooperative Oncology Group (ECOG) performance scale (PS) score of0–1

4. Failure to respond to second-line treatment (patients with negative driver genes were evaluated for progression or intolerance after ≥ two different regimens of chemotherapy,and those with positive driver genes [EGFR mutation or ALK rearrangement] were evaluated for progression or intolerance after treatment with TK inhibitors and ≥ one regimen of chemotherapy)

5. A measurable lesion based on the RECIST criteria

6. The expected survival time≥12 weeks

7. Normally functioning major organs

8. Hemoglobin >100 g/L; platelet count > 100*10^9^/L; number of neutrophils >1.5 × 10^9^/L

9. Serum creatinine ≤1.25×upper limits of normal (ULN) or creatinine clearance rate > 60 mL/min.

10. Total bilirubin (TBIL) ≤1.5× ULN; as partate aminotransferase (AST)and alanine aminotransferase (ALT or SGPT) ≤2.5×ULN; alkaline phosphatase ≤ 5×ULN

11. Doppler ultrasound evaluation: left ventricular ejection fraction (LVEF)≥50%

12. No interstitial pneumonia or history of interstitial pneumonia

13. Patients or their family members who signed the informed consent

14. Female patients of childbearing age who agreed to use contraceptives (such as intrauterine devices, birth control pills, or condoms) in the study period and for six months after the end of the drug treatment; the serum or urine test indicated no pregnancy in the seven days prior to the study, and patients who were not lactating; male patients who agreed to use contraception during the study period and for six months after the end of the study period.

*Exclusion criteria*

1. Previously used anlotinib or S-1

2. Small-cell lung cancer (including small-cell carcinoma and non-small-cell carcinoma mixed lung cancer)

3. Presence of malignancies currently or in the past 5 years

4. Unable to intake medication orally (such as the inability to swallow, chronic diarrhea, intestinal obstruction.)

5. EGFR mutation-positive or ALK rearrangement-positive and no use the relevant targeted drugs

6. Brain metastases with symptoms or controlled symptoms for <two months

7. Central, empty lung squamous cell carcinoma or NSCLC with hemoptysis (>50 mL/day);

8. Severe and/or uncontrolled disease, including:

a. Uncontrolled high blood pressure (systolic blood pressure ≥ 150 mmHg and diastolic blood pressure ≥ 100 mmHg)

b. Myocardial ischemia or myocardial infarction and arrhythmia (QTc≥480 ms and ≥ 2 levels of congestive heart failure according to the New York Heart Association [NYHA]classification)

c. Active or uncontrollable serious infection (≥Common Terminology Criteria Adverse Events[CTCAE] level 2 infection)

d. Liver cirrhosis, decompensate liver disease, active hepatitis, or chronic hepatitis, which needs to be treated with antiretroviral therapy

e. Renal failure, which requires hemodialysis or peritoneal dialysis

f. History of immunodeficiency, including human immunodeficiency virus (HIV) or other acquired, congenital immunodeficiency disease, or history of organ transplantation

g. Poor control of diabetes (fasting blood glucose [FBG]> 10 mmol/L)

h. Routine urine test protein ≥++ and confirmed 24-hour urine protein> 1.0 g

i. Seizures that require treatment

9. Imaging studies shows that the tumor has invaded important vessels or the researchers determine that the tumor is likely to invade important blood vessels caused by fatal bleeding during the follow-up

10. Regardless of the severity, patients with any sign or medical history of bleeding four weeks prior to allocation, patients with any bleeding events ≥ CTCAE level 3, unhealed wounds, ulcers, or fractures

11. Arterial/venous thrombotic events(such as cerebrovascular accident [temporary ischemic attack], deep vein thrombosis, and pulmonary embolism) six months before allocation

12. Extra-field radiotherapy (EF-RT) performed four weeks before allocation, restricted radiotherapy performed for assessing tumor lesions two weeks before allocation or those prepared to receive local treatment (radiotherapy or radiofrequency ablation) at the time of the study; those undergoing palliative treatment, such as radiotherapy for bone metastases, will not be excluded.

13. Participated in other anti-tumor drug trials within four weeks

14. A history of psychotropic medicine abuse or mental disorders

15. Diagnosed with a disease that will severely endanger health or influence the completion of this study

16. Pregnant or lactating women

17. Considered unfit for inclusion by other physicians

*Data collection and management*

The following data will be collected from the patients: name, gender, age, lesion location, pathological type of cancer, clinical stage, drug dose and frequency, and examination results. We will review and analyze the data. We will acquire the data using an electronic data management system and generate a data base. We will perform statistical analysis before data audit.

*Sample size calculation*

We estimated the sample size using Simon’s phase II clinical trial design: with α = 0.05, power β = 0.2, and Pl– P0 = 0.20. The required number of patients was estimated to be ≥29based on the objective response rate of anlotinib monotherapy.

*Dose and frequency*

Anlotinib: orally 12mg once-a-day before breakfast for two consecutive weeks, then withdrawn for one week, with a 21-day course of treatment.

S-1: orally 70mg/m^2^/day, twice-a-day after meals for two consecutive weeks, then withdrawn for one week, with a 21-day course of treatment.

If the efficacy was assessed as SD, PR, and CR after six cycles; anlotinib was maintained until disease progression or death.

*Assessment of the primary and secondary endpoints*

Adverse events were recorded in accordance with the requirements of Medical Dictionary for Regulatory Activities (Med DRA). The severity of adverse events was graded according to the National Cancer Institute Common Terminology Criteria(NCI-CTC). The toxicity of the treatment, including acute and chronic toxicity, was evaluated during treatment and follow-up (Table 1).Any serious adverse drug reaction was promptly reported to the hospital ethics committee. PFS was defined as the date from randomization to tumor progression or death. Duration of response was assessed in patients who achieved a response and was defined as the time from the date of the first documented response to the date of the documented progression or death from any cause. Disease control was defined as the proportion of patients who achieved a CR, PR, or SD.

*Criteria for study discontinuation*

1. Withdrawal of informed consent

2. To ensure patients’ safety, the researchers may decide to discontinue the study

3. In case of an adverse event, researchers or patients may choose to discontinue the study

4. Researchers’ discretion

*Ethics*

The study was approved by the Ethics Committee of Mianyang Central Hospital, Sichuan, China (Number: S2019001). The study was supervised and managed by the ethics committee.

*Status*

We registered in the Chinese Clinical Trial Registry(Number: ChiCTR1900020948).Recruitment was initiated in January 2019, with a planned recruitment period of two years.

**Table 1 T1:** Evaluation of the Treatment Process

Evaluation		Time
Hematological examination	Hemoglobin, platelets, white blood cells, neutrophils	Once a week
Biochemical tests	Biochemical and electrolyte	Once a week
Gastrointestinal effect	Nausea and vomiting	Once a week
Imaging examination	CT scan	Tumors were assessed before treatment, after 2 cycles, 4 cycles, 6 cycles, and during the follow-up every 3 months until disease progression or death.
	Brain MRI	Before treatment and every 3 months during the treatment and follow-up

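### Exclusion 8a joins its two blood pressure limits with 'and', so read as printed a patient over only one limit does not meet the numeric rule (minor)

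*Protocol article*

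**What the plan says.** In the protocol article, Materials and Methods, Exclusion criteria, item 8 opens with "Severe and/or uncontrolled disease, including" and then lists conditions a to i. Item 8a is "Uncontrolled high blood pressure (systolic blood pressure ≥ 150 mmHg and diastolic blood pressure ≥ 100 mmHg". This is the only blood pressure limit in the document.

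Three other places could bear on a hypertensive patient, and none carries a number for blood pressure. Inclusion criterion 7 asks for "Normally functioning major organs" without a limit. Exclusion 15 covers a diagnosed disease that would seriously threaten health or interfere with completing the study. Exclusion 17 leaves unfitness to a physician's view.

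The Study design section says that patients come from several hospitals in one province, and that everyone who meets the inclusion criteria and consents will take part.

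**The concern.** A limit meant to identify uncontrolled hypertension would normally be met when either pressure is too high. Joined by 'and', it is met only when both are. Isolated systolic or isolated diastolic elevation, however marked, then falls outside the one numeric rule that the protocol provides.

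The protocol itself treats uncontrolled high blood pressure as a reason not to enrol. If a site applies the bracket literally, the number does not serve that purpose for these patients. If one site reads it literally and another reads it as 'or', the same patient could be turned away at one hospital and accepted at the other. What is at stake is patient safety at entry and uniform screening. No statistical property of the design is in question.

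**Working it through.** **Inputs.** From exclusion 8a: systolic limit 150 mmHg, diastolic limit 100 mmHg, connective 'and'. The blood pressure pairs below are illustrations chosen to test the rule; they are not data from the document.

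**Formula.** Let S = (systolic ≥ 150) and D = (diastolic ≥ 100). The printed rule excludes when S and D are both true. The alternative rule excludes when S or D is true. The two rules differ exactly for patients with one of S and D true and the other false.

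**Results.**

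| Blood pressure (mmHg) | S | D | Excluded under 'and' (printed) | Excluded under 'or' |
|---|---|---|---|---|
| 190/95 | true | false | no | yes |
| 145/110 | false | true | no | yes |
| 220/99 | true | false | no | yes |
| 149/130 | false | true | no | yes |
| 150/100 | true | true | yes | yes |
| 160/105 | true | true | yes | yes |
| 149/99 | false | false | no | no |

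Whenever diastolic is 99 mmHg or below, D is false, so the printed rule cannot be met at any systolic value. Likewise, whenever systolic is 149 mmHg or below, it cannot be met at any diastolic value.

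**Does usage elsewhere settle what 'and' means?** It points both ways.

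- Item 8h of the same list reads "Routine urine test protein ≥++ and confirmed 24-hour urine protein> 1.0 g". Here 'and' is a genuine joint test: a dipstick finding confirmed by a 24-hour collection. A reader of item 8 has reason to carry that meaning back to 8a.
- Study design has "assessed as stable disease (SD), partial response (PR), and complete response (CR) after six cycles", and Dose and frequency has "If the efficacy was assessed as SD, PR, and CR after six cycles". One patient cannot hold all three response categories at once, so 'and' there has to mean 'or'.

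The text therefore does not fix the meaning of 8a. A slip is the likelier explanation, but the literal reading is available to a site.

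**Effect on the design.** Sample size calculation uses a significance level of 0.05, β of 0.2, a response-rate difference of 0.20 and the monotherapy response rate. No eligibility limit enters it, so the figure of 29 does not change with either wording.

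**The case against.** The strongest reply is that nobody would be misled. The excluded condition is uncontrolled high blood pressure, under a heading whose list is introduced as non-exhaustive. An investigator facing 190/95 or 220/99 mmHg would call that uncontrolled whatever the bracket says, and exclusions 15 and 17 give further grounds to refuse entry. The article plainly uses 'and' for alternatives elsewhere, so the list reading of 8a is natural. The documents also never say that anlotinib raises blood pressure.

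Much of this stands. The routes by judgement are real, and they mean that enrolling such a patient is possible, not certain. A reader might infer that the trial will admit severely hypertensive patients; the documents do not support that. Nor is the point built on any property of the drug. It rests on the protocol's own decision to exclude uncontrolled hypertension.

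What does not stand is that this makes the printed number right. If 'or' was meant, the criterion is misprinted. If 'and' was meant, it leaves out isolated elevation of either pressure. The correction is the same in both cases. A numeric limit exists so that several hospitals need not each decide case by case, and a general discretion clause is a weak corrective when a specific number points the other way.

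**Conclusion.** The point holds, as a minor one. As printed, the numeric rule in 8a misses every patient over exactly one of the two limits, and for those patients only judgement remains. This assumes that a site reads the bracket literally, which the text allows but does not compel. The document gives no basis for how many patients would exceed exactly one limit, so no frequency is claimed.

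Two wider readings should not be drawn. A reader might infer that 8b shares the defect, because its bracket has "QTc≥480 ms and ≥ 2 levels of congestive heart failure according to the New York Heart Association". That bracket can equally be a compressed list, and the text does not settle how its terms group, so it is a matter of clarity and forms no part of this finding. A reader might also infer some effect on the objective response rate, the sample size or the analysis; nothing in the document supports that.

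**What to change.** In exclusion 8a, replace the 'and' between the two limits with 'or', so that the bracket reads: systolic blood pressure ≥150 mmHg or diastolic blood pressure ≥100 mmHg. Leave 8h as it is, because its 'and' is a confirmation step.

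The cost is a one-word amendment, notified to the sites, and possibly a few more screen failures. The planned 29 patients and the analysis stay as they are.

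### As written, the article puts the statistical analysis before the data audit; the order should be reversed, or the sentence corrected if it is a wording slip

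*Protocol article*

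**What the plan says.** The relevant text is in the protocol article, Materials and Methods, under Data collection and management. After listing the items to be collected, it makes three short statements. The first is "We will review and analyze the data", which names a review but does not place it in time relative to the audit. The second says that an electronic system will be used to build the database, without saying when that database is closed. Only the third fixes an order, and it puts the analysis first: "We will perform statistical analysis before data audit". The article does not say what the audit consists of, which version of the data feeds the reported result, or whether the analysis is repeated afterwards.

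The setting is given in the same part of the article. Under Objectives, "The primary endpoint is the ORR". Under Study design, response is assessed by RECIST in 29 patients recruited at several hospitals, and "There will be no randomized control group in this study".

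**The concern.** An audit protects a result only if its corrections are made before the result is computed, by people who do not yet know it. With the order reversed there are two possibilities. Either the corrections do not reach the result, and the audit does nothing for the ORR, or they do reach it and are decided by people who already know which way each change moves the answer.

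This trial has little to absorb such errors. The primary endpoint is a count of responders among 29 patients, to be compared with what is known of anlotinib alone. There is no concurrent arm in which similar misclassification might offset it, and the article describes no masking. A wrong response call passes straight into the estimate.

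This is not a detail left to a fuller document. The article states a rule, and the rule is wrong if followed. A statistical analysis plan with the usual order would contradict the published sentence, which would still need correcting.

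**Working it through.** **1. Does any other text change the order?** The three data-handling statements set side by side:

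| Step | Timing stated in the article |
|---|---|
| Review of the data | None relative to the audit |
| Building the database | No lock or freeze mentioned |
| Statistical analysis | Before the audit |

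The sections on study design, endpoint assessment, discontinuation, ethics and status do not return to the subject. The stated order stands uncorrected.

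**2. What one patient is worth.** This needs only n = 29.

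- Shift per reclassified patient: 1/29 = 0.0345, or 3.4 percentage points.
- Example: 5/29 = 17.2%, exact (Clopper-Pearson) 95% interval 5.8% to 35.8%; 6/29 = 20.7%, interval 8.0% to 39.7%.

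The two intervals overlap almost entirely, and both contain 9.2% and 10%. What one patient can change is the point estimate and any pass/fail decision, not the broad range of plausible rates.

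**3. Reproducing the article's sample size.** The inputs under Sample size calculation are "with α = 0.05, power β = 0.2, and Pl– P0 = 0.20" and "The required number of patients was estimated to be ≥29based on the objective response rate of anlotinib monotherapy". The Introduction gives the monotherapy figure: "the objective response rate (ORR) was only 9.2" percent. The article does not state the null rate P0, the sidedness of alpha, the stages or the decision boundary.

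Assume P0 = 0.10 (9.2% rounded), P1 = 0.10 + 0.20 = 0.30, one-sided alpha 0.05 and power 0.80. For a two-stage design with n1 patients in stage 1, a stop at r1 or fewer responses, and success above r responses in n:

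P(success | p) = Σ over x from r1+1 to n1 of P(X1 = x) × P(X2 ≥ r + 1 − x), with X1 ~ Bin(n1, p) and X2 ~ Bin(n − n1, p).

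The search for the smallest expected sample size under P0 gives r1/n1 = 1/10 and r/n = 5/29. Alpha is 0.047 and power 0.805. The article's 29 is reproduced, with success at 6 or more responses.

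**4. Illustration at that boundary.** The extreme case is that every result one response from the boundary is moved across it once seen:

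| Rule in effect | P(success) at 0.10 | P(success) at 0.30 |
|---|---|---|
| Success at 6 or more | 0.047 | 0.805 |
| Every 5 moved to 6 | 0.102 | 0.837 |
| Every 6 moved to 5 | 0.018 | 0.739 |

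**5. How far the boundary depends on the assumptions.**

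- With P0 = 0.092 and P1 = 0.292 unrounded, the optimal design needs 31 patients, not 29. The 1/10, 5/29 rule then has alpha 0.033 and power 0.785.
- With P0 = 0.10 and P1 = 0.30 but one-sided alpha 0.025, the minimax design is 2/18, 6/29 (alpha 0.021, power 0.801). It also has 29 patients, but success needs 7 responses.

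So a total of 29 does not by itself identify 6 as the threshold. Step 2 holds regardless; steps 3 and 4 are illustration.

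**The case against.** **It may be a wording slip.** The article has comparable ones: beta of 0.2 is labelled as power, and progression-free survival is timed from randomization in a trial without a randomized control group. A slip is a likely explanation, and this stands. It does not rescue the sentence, because nothing in the article tells a reader or analyst to do the opposite.

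**The audit is undefined and a review is mentioned.** The audit could be a later oversight check rather than data cleaning, with some checking done under the review. This also stands. The article does not show that response calls, dates and adverse events would go into the analysis wholly unchecked.

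**The reported ORR need not come from unaudited data.** A reader might infer that it does, but the article does not say which dataset feeds the report or whether the analysis is rerun. The two harms are also alternatives: if corrections reach the result, the final ORR is not unaudited; if they do not, they cannot steer it.

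**The order causes only part of the risk.** In an uncontrolled trial of 29 patients, investigators can keep a running count of responders whichever step comes first. That is true, so auditing first reduces the exposure without removing it.

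**The size argument is generic.** One patient is 3.4 points in any trial of 29, and the article gives no basis for how many calls an audit would change. The figure shows sensitivity to an error, not how likely one is.

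**Conclusion.** The point holds in a limited form. The article states an order of work that is wrong if followed, and nothing in it corrects that order. Followed literally, the ORR would be computed before the audit, and later corrections would either miss the result or be made in its light. Each reclassified patient is worth 3.4 percentage points, which rests only on n = 29.

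The one-patient gap between failure at 5 responses and success at 6 rests on P0 = 0.10, P1 = 0.30, one-sided alpha 0.05 and Simon's optimal design, none of which the article states. The rise in type I error from 0.047 to 0.102 further assumes that every 5-response result is altered after being seen. It is an extreme case, not an estimate.

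It would go too far to say that an analysis flaw has been established, or that the sponsor intends to adjust data once results are known. Given the possible slip and the undefined audit, this is a sentence that must be corrected or clarified, with moderate rather than high confidence that it describes the intended procedure.

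**What to change.** Replace the sentence on the order of analysis and audit with:

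*Data audit and query resolution will be completed and the database locked before statistical analysis; any later change will be documented and its effect on the ORR reported.*

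If the audit is meant as a later oversight check, separate from data cleaning, say so in a further sentence so that the two are not confused.

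The cost is one sentence and a slightly later start to the analysis. The audit is already planned, and the sample size of 29, alpha, power, endpoint and patient care are unchanged.

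### CT after cycles 2, 4 and 6 and then only every 3 months records PFS and duration of response coarsely and late; an interval-censored estimate on one calendar grid would correct for this without extra scans

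*Protocol article*

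**What the plan says.** The schedule is stated consistently in the Abstract, in Study design and in Table 1. Study design has CT "before the treatment, after two, four, and six cycles, and during follow-up every 3 months until disease progression or death"; Table 1 agrees: "Tumors were assessed before treatment, after 2 cycles, 4 cycles, 6 cycles, and during the follow-up every 3 months until disease progression or death". Under Dose and frequency, both drugs are given "for two consecutive weeks, then withdrawn for one week, with a 21-day course of treatment", so the first three on-treatment scans fall nominally at weeks 6, 12 and 18. Patients with stable disease or a response after six cycles stay on treatment: "anlotinib will be maintained until disease progression or death". The scan interval therefore widens during maintenance. Brain MRI every 3 months does not close the gap for disease outside the brain.

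Under Objectives, ORR is primary, and "The secondary endpoints are progression-free survival (PFS), duration of response, proportion of disease control, and safety". Under Assessment of the primary and secondary endpoints, "PFS was defined as the date from randomization to tumor progression or death". Duration of response is "the time from the date of the first documented response to the date of the documented progression or death from any cause". Study design states that there is no randomised control group. No expected median PFS is given anywhere.

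**The concern.** Progression found on imaging is known only to lie between the last clear scan and the first scan that shows it. If it is dated at the second of these, every such event is recorded late, and the recorded times can take only a few values. Here the widest gap opens at 4.1 months and closes at 7.1 months. A true median inside that gap would be reported at its far end.

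In a randomised trial both arms share the scan grid, and much of this lateness cancels in the comparison. In a single-arm trial it does not. A reader who sets the reported median PFS or duration of response beside results scanned on another schedule would be comparing grids as well as treatments. The first three scans are also tied to completed cycles, so patients with delayed cycles are on a different grid from the rest.

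**Working it through.** **Inputs.** CT schedule and cycle length are from the article. It gives no median PFS, so true medians of 3 to 8 months are assumed. Further assumptions: exponential PFS, progression dated at the detecting scan and, in the base case, all events detected by scan.

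**The plan's own figure.** The only relevant stated figure is N = 29, which rests on ORR. The Introduction gives 9.2% for monotherapy. Rounding to p0 = 0.10, with p1 = 0.30, α = 0.05 and power 0.80, Simon's optimal design stops if at most 1 of 10 respond and needs more than 5 of 29 overall (exact α 0.047, power 0.805). N = 29 is reproduced and does not depend on the later scan interval.

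**Scan times.** One month = 365.25/12/7 = 4.348 weeks.
- Weeks 6, 12, 18 = 1.38, 2.76, 4.14 months.
- Next scan: 4.14 + 3 = 7.14 months (week 31.0), then 10.14.

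**Recorded median.** This is the first scan time g with S(g) ≤ 0.5, whatever the shape of the curve. Any true median just above 4.14 and up to 7.14 months therefore reads 7.14. The step is sharp: 4.1 reads 4.1, and 4.2 reads 7.1.

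**Mean lateness.** With scan times g₁, g₂, … and g₀ = 0, mean lateness = Σ (gⱼ − gⱼ₋₁)·S(gⱼ₋₁) − m/ln 2, where S(t) = 0.5^(t/m). For m = 5.0:
- first three intervals: 1.380 × (1 + 0.826 + 0.682) = 3.461
- 3-month intervals: 3 × 0.563 / (1 − 0.5^0.6) = 4.967
- mean true PFS: 5/0.6931 = 7.214
- lateness: 3.461 + 4.967 − 7.214 = 1.21 months

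The table gives recorded median, then mean lateness, in months. The delay column assumes one extra week per two cycles (scans at weeks 7, 14, 21, then about 34).

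| True median | Protocol grid | Delay | Even 6-week grid |
|---|---|---|---|
| 3.0 | 4.1; 1.09 | 3.2; 1.12 | 4.1; 0.73 |
| 4.0 | 4.1; 1.16 | 4.8; 1.18 | 4.1; 0.72 |
| 4.5 | 7.1; 1.19 | 4.8; 1.21 | 5.5; 0.71 |
| 5.0 | 7.1; 1.21 | 7.8; 1.23 | 5.5; 0.71 |
| 6.0 | 7.1; 1.25 | 7.8; 1.26 | 6.9; 0.71 |
| 7.0 | 7.1; 1.28 | 7.8; 1.29 | 8.3; 0.71 |
| 8.0 | 10.1; 1.31 | 10.8; 1.31 | 8.3; 0.70 |

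**Exactly dated deaths.** If 20% of events are deaths (assumed), the recorded median x solves 0.2·(1 − S(x)) + 0.8·(1 − S(4.14)) = 0.5, capped at 7.14. True medians of 4.2, 4.5 and 5.0 read about 4.4, 6.2 and 7.1.

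**N = 29, true median 5.0, all events scan-detected.** In simulation the sample median reads 2.76, 4.14, 7.14, 10.14 or 13.14 months in 2.0%, 22.6%, 67.5%, 7.8% and 0.1% of trials. Its average is 0.020 × 2.76 + 0.226 × 4.14 + 0.675 × 7.14 + 0.078 × 10.14 + 0.001 × 13.14 = 6.6 months, with root mean squared error (RMSE) 2.3. An interval-censored Weibull fit to the same kind of data averages 5.0 to 5.1, with RMSE 1.1 to 1.2. The simulated data were exponential, so the Weibull form was correct by construction.

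**Duration of response.** A response first seen at week 18 cannot show scan-detected progression until about 13 weeks later; one first seen at week 6 or 12 can do so after 6 weeks.

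**The case against.** Several points on the other side stand.

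- The choice between Kaplan-Meier and an interval-censored estimator belongs in an analysis plan, which is not shown, and a condensed article commonly omits visit windows. So the absence of a stated method is not a fault. What the article does fix is the schedule, and the coarseness follows from that.
- The 7.1-month reading needs a true median between 4.1 and 7.1 months, which the article does not claim. At 4.0 months the protocol grid and an even 6-week grid both read 4.1.
- Anchoring scans to the calendar leaves the 13-week gap in place. Only the interval-censored analysis addresses that.
- The affected endpoints are secondary.

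Three stronger readings are tempting but unsupported.

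- A reader might infer that toxicity delays lengthen PFS, so that a more toxic regimen looks better. The table does not bear this out: at a true 4.5 months the assumed delay lowers the recorded median from 7.1 to 4.8, while at 4.0 and 5.0 it raises it. Mean lateness changes by about 0.03 months or less, and by less than 0.1 even with a week's delay in every cycle. The article gives no delay rate.
- A reader might infer that the bias favours the combination over monotherapy. That depends on how the monotherapy patients were scanned, which the article does not say. Its stated expectation against monotherapy concerns ORR.
- A reader might infer that the scan grid rather than the tumour sets the result. The tumour decides which interval contains progression, and deaths can be dated exactly.

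**Conclusion.** The point holds for the secondary time-to-event endpoints, as a cheap improvement. If progression is dated at the detecting scan, PFS is recorded about 1.1 to 1.3 months late on average, against about 0.7 on an even 6-week grid. A true median between 4.1 and 7.1 months is reported as about 7.1, less if some events are deaths. Duration of response shares the coarse end date. With no control arm the lateness does not cancel.

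The lateness figures rest on exponential PFS and assumed medians of 3 to 8 months; the 4.1-to-7.1 step needs only the nominal scan times and scan-dated progression. Dose delays move the scan dates but barely change mean lateness. No toxicity-driven bias and no direction relative to monotherapy is shown. ORR and N = 29 are unaffected.

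**What to change.** 1. Report PFS and duration of response with an interval-censored estimate beside Kaplan-Meier: each progression lies between the last progression-free scan and the first scan showing progression, and deaths are dated exactly. Turnbull's estimator needs no distributional form; a Weibull model gives a smoother median at the price of one.
2. Schedule the same CTs by calendar week from first dose (weeks 6, 12 and 18, then every 3 months), whatever the cycle dates, so that all patients share one grid. This does not narrow the gap after week 18; it makes the recorded times comparable between patients. The PFS start date, now given as randomisation in a trial without it, should be reconciled with that origin.

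Cost: a change of wording, one extra analysis (checking that SPSS, the package the article names, can run it), a modelling assumption if Weibull is used, and probably a shorter reported median PFS. No extra scans and no change to the sample size.
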